### Investigational product

Celltrion Healthcare will provide rituximab (Truxima®) free of charge for this study. The investigational rituximab will be stored in a secure area in accordance with local regulations.

### Machine learning algorithm

A machine learning algorithm was developed to predict the risk of rituximab underdosing (concentration <2 µg/mL at month 3).^24^ The algorithm is based on a support vector machine (SVM) with a polynomial kernel and was selected after comparison with several supervised models, including logistic regression, random forests and artificial neural networks. The SVM was chosen for its ability to handle data with small sample sizes while maximising the separation between classes in a high-dimensional space.

The performance of the models was assessed by 10-fold cross-validation on the training set (75% of the data). The SVM achieved an accuracy of 79.4%, outperforming logistic regression (70.6%), random forests (73.5%) and artificial neural networks (68.3%). In terms of sensitivity and specificity, the SVM showed a balanced performance (84.6% and 72.7%, respectively, on the test set) compared with the results obtained by logistic regression (sensitivity 75% and specificity 65%) and random forests (sensitivity 78.1% and specificity 68.2%). The SVM also showed an F-score of 81.5%, highlighting its overall effectiveness in categorising patients.

The model’s input variables were selected using a forward-backward approach, systematically assessing the impact of adding or removing a variable on predictive performance. The variables selected included age, sex, body surface area (BSA), anti-PLA2R1 antibody titre at day 0 (optional variable), serum albumin and serum creatinine at days 0 and 15. Prior to model training, data were preprocessed with K-nearest neighbour imputation of missing values, followed by standardisation to ensure homogeneous scaling of continuous variables.

### Treatment arms

#### Experimental strategy

For patients randomised to the experimental arm, the iRITUX multidisciplinary staff will run the algorithm and make a recommendation to the referring nephrologist based on the risk of rituximab underdosing at month 3.

Patients with a risk between 0% and 50% will receive 1 g×2 (day 0 and day 15).Patients with a risk between 51% and 75% will receive 1 g×3 (day 0, day 15 and day 30).Patients with a risk between 76% and 100% will receive 1 g×4 (day 0, day 15, day 30 and day 45).

If the opinion of the referring nephrologist contradicts the result generated by the iRITUX algorithm, the opinion of the patient’s treating nephrologist will prevail in all cases.

#### Control strategy

Patients randomised to the control arm will receive two courses of rituximab at a dose of 1 g on days 1 and 15.

To improve compliance, patients will be contacted by telephone before each treatment. A medical consultation is also scheduled for all rituximab injections.

### Relevant concomitant care

Medications not listed in the exclusion criteria may be administered at the investigator’s discretion. The investigator will record all concomitant medications taken by the participant in the appropriate section of the case report form.

### Sample size

Sample size calculation was performed according to the sequential design method in order to consider the implementation of three interim efficacy analyses. The sample size was calculated with SAS applying the SEQDESIGN procedure, considering the risk of increasing the alpha risk due to multiple analyses. The method used in our case was the O’Brien-Fleming type of boundary (design method=obf) to maximise our chance of stopping the study at the final analysis, if we cannot reach a positive conclusion during the interim analyses.

The criteria applied for the sample size calculation were a total alpha risk at 0.025, with an estimated result of 75% remission in the personalised arm (number of rituximab doses defined by the algorithm) versus 50% in the standard arm (rituximab 1 g×2) and a one-sided sample test for the difference between two binomial proportions. These assumptions about remission rates are based on observations from a retrospective cohort comparing remission rates in patients with rituximab underdosing with those in patients without rituximab underdosing.^10^

Finally, to maintain the total alpha risk at 0.025 and the total beta risk at 0.2 with four analyses, we need to enrol 130 patients in our study, which accounts for a 5% rate of lost to follow-up (anticipated as minor in this study as patients are intensively followed for this pathology).

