Nowadays, machine learning algorithms are increasingly used in medicine and especially in pharmacology to predict the exposure to a drug, the initiation dose or the interval between two infusions. We have developed a machine learning algorithm to predict the risk of rituximab underdosing.^24^ Based on age, sex, body surface area, anti-PLA2R1 antibody titre at day 0, serum albumin at day 0 and at day 15 and serum creatinine at day 0 and at day 15, this algorithm demonstrated its ability to predict rituximab underdosing at 3 months with an accuracy, sensitivity and specificity of, respectively, 79.4%, 78.7% and 81.0%. To validate the clinical relevance of our algorithm, we analysed the outcome of 45 patients with membranous nephropathy treated with rituximab. We retrospectively analysed the cumulative doses of rituximab received to achieve clinical remission and the time to achieve clinical remission according to the initial probability of rituximab underdosing proposed by our algorithm. Patients with a high initial probability of rituximab underdosing (>50%) had a longer time to remission (probability of rituximab underdosing ≤50%: 4.2±1.8 months vs 51%–75%: 8.4±4.6 months vs >75%: 10.7±5.9 months; p=0.002) and received higher cumulative doses of rituximab (probability of rituximab underdosing ≤50%: 2.0±0.0 g vs 51%–75%: 2.7±0.9 g vs >75%: 3.6±1.6 g; p=0.001).^24^

To prospectively evaluate our algorithm, we planned a multicentre, randomised study to evaluate the superiority and safety of an algorithm-guided rituximab regimen versus a standard regimen in patients with membranous nephropathy.

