#### Benefits

##### At the individual level

20%–40% of patients with membranous nephropathy do not respond to a first course of rituximab.^9^ Persistent nephrotic syndrome may be complicated by arterial or venous thrombosis, increased cardiovascular risk, immunodeficiency and chronic renal failure. The persistence of nephrotic syndrome may also affect the quality of life and socioeconomic integration of patients. Patients with nephrotic syndrome have reduced drug bioavailability due to urinary loss of rituximab compared to other non-proteinuric autoimmune diseases treated with rituximab.^11^ We have previously shown that patients with undetectable serum rituximab levels at month 3 were less likely to achieve clinical remission at months 6 and 12.^10^ Additional early doses of rituximab may increase the bioavailability of the drug, increasing the likelihood of early remission by month 6. Repeated doses of rituximab, up to cumulative doses of 3000–6000 mg, according to autoantibody immunomonitoring, have been shown to be effective in inducing clinical remission while being safe.^17 23^ Achieving early remission would help to (1) preserve renal function; (2) preserve patients’ quality of life and socioeconomic integration and (3) limit cardiovascular and thromboembolic risks.

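### The 75% versus 50% planning rates come from a comparison of patients without and with underdosing and are used as arm rates with no conversion, so the stated 80% power does not follow from its stated basis

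*Protocol article*

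**What the plan says.** The Sample size section of the protocol article sets "an estimated result of 75% remission in the personalised arm (number of rituximab doses defined by the algorithm) versus 50% in the standard arm", with one-sided alpha 0.025. It concludes that, "to maintain the total alpha risk at 0.025 and the total beta risk at 0.2 with four analyses", 130 patients are needed, including 5% lost to follow-up. On the source of the rates it says: "These assumptions about remission rates are based on observations from a retrospective cohort comparing remission rates in patients with rituximab underdosing with those" of patients who were not underdosed.

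Other sections determine how such a contrast carries over to the arms:

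- Control strategy: every control patient receives two 1 g infusions, whether or not that regimen underdoses them.
- Experimental strategy: "Patients with a risk between 0% and 50% will receive" the same two infusions. Only patients above 50% risk are treated differently, and the treating nephrologist may overrule the algorithm.
- Introduction: the algorithm's performance is given as "accuracy, sensitivity and specificity of, respectively, 79.4%, 78.7% and 81.0" per cent. The Machine learning algorithm section gives a test-set sensitivity of 84.6%, specificity of 72.7% and F-score of 81.5%.
- Benefits, At the individual level: 20%–40% "of patients with membranous nephropathy do not respond to a first course of rituximab", with no time point.

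**The concern.** A difference between underdosed and not-underdosed patients becomes a difference between arms only if every control patient is underdosed and every such patient in the experimental arm is detected and fully corrected. Neither is assumed in the protocol. The control arm takes all eligible patients, so its expected rate lies between the two group rates. Part of the experimental arm is treated exactly like control and can add nothing to the difference.

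The beta of 0.2, the sample size and the group-sequential plan all rest on the 25-point difference. Enrolment is planned to take six years. If the real arm difference is well below 25 points, a null result would be a likely outcome even with a useful algorithm, and could be misread as evidence that the algorithm does not work.

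**Working it through.** **1. The plan's own figure.** The stated one-sided levels (0.0002248, 0.00209, 0.00969, 0.02144) correspond to z = 3.509, 2.864, 2.338 and 2.025. They match an O'Brien-Fleming boundary at information fractions 1/3, 1/2, 3/4 and 1, with total alpha 0.025. For 75% vs 50%, using the average proportion 0.625:

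- fixed n per arm = (1.960 + 0.842)² × 2 × 0.625 × 0.375 / 0.25² = 58.9, so about 118 in total;
- times the sequential inflation factor 1.024 = 120.6;
- divided by 0.95 = 127, within 3% of 130.

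Power at 75% vs 50% is 81% (123.5 evaluable, pooled variance) to 85% (130 evaluable, unpooled variance). The arithmetic is sound; the question is the effect size put into it. Power ranges below use the same two variants.

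**2. From groups to arms.** Let f be the share underdosed on two 1 g infusions and s the algorithm's sensitivity. Take 50% remission if underdosed and 75% if not, and assume that a detected patient is fully corrected to 75%.

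- Control rate = 75 − 25f
- Arm difference = 25 × f × s, at most 25f

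This also assumes that extra doses do not help patients flagged in error. Overruling of the algorithm is ignored; where it withholds extra doses from detected patients, the difference shrinks further.

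**3. The underdosed share.** It is not printed, so it is inferred from the performance figures:

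- Introduction: 78.7% = 37/47, 81.0% = 17/21 and 79.4% = 54/68, so f = 47/68 = 69%.
- Test set: 84.6% = 11/13, 72.7% = 8/11 and F-score = 22/27 = 81.5%, so f = 13/24 = 54%.
- Pooled: 60/92 = 65%.

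These are small samples and integer reconstructions, so f is treated as an assumption with a range.

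**4. Results at N=130 with the stated boundaries.**

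| f | Sensitivity | Control | Algorithm arm | Difference (points) | Power |
|---|---|---|---|---|---|
| 0.54 | perfect | 61.5% | 75.0% | 13.5 | 36–38% |
| 0.54 | 84.6% | 61.5% | 72.9% | 11.4 | 26–28% |
| 0.69 | perfect | 57.8% | 75.0% | 17.3 | 52–55% |
| 0.69 | 78.7% | 57.8% | 71.3% | 13.6 | 34–36% |
| 0.40 | perfect | 65.0% | 75.0% | 10.0 | 22–23% |
| 0.80 | perfect | 55.0% | 75.0% | 20.0 | 63–68% |
| 1.00 | 78.7–84.6% | 50.0% | 69.7–71.2% | 19.7–21.2 | 60–70% |

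With perfect targeting, 80% power needs f of about 0.93–0.99. With the reported sensitivities it is not reached even at f = 1.

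**5. What would restore 25 points.** If 65% of patients are treated differently, they must gain 25/0.65 = about 38 points on average. If the treated-differently share is the flagged share in the reconstructed tables ((41 + 14)/92 = 60%), they must gain 25/0.60 = about 42 points. If 75% and 50% were instead derived arm rates, the gap between underdosed and not-underdosed patients would have to be 25/(0.69 × 0.787) = 46 to 25/(0.54 × 0.846) = 55 points. The article states no such gap.

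**The case against.** The strongest reply is that the two group rates are not in the article. The section says only that its assumptions are based on the cohort, so 50% and 75% may already be derived arm rates, with the derivation left to the full protocol. That cannot be excluded, and it is why the result is conditional on the plain reading.

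A second reply uses the Introduction's times to remission by risk class: 4.2±1.8, 8.4±4.6 and 10.7±5.9 months. Under normal, lognormal or gamma shapes these give about 84–86%, 30–35% and 19–22% remission by month 6. With 60% of patients above 50% risk and the two upper classes weighted equally, the control rate is close to 50%. Closing three quarters of a gap of about 58 points would yield 0.75 × 58 × 0.60 = 26 points and power of about 84–87%; closing half would give about 47–50%. The shapes and weights are assumptions, the cohort has 45 patients, the times may describe remitters only, and higher-risk patients received more drug. Still, it shows that a 25-point arm difference is possible. It does not rescue the section as written, which invokes the underdosing contrast and no such gain.

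Third, the 75% ceiling is assumed here: extra doses might lift remission above it or help patients flagged in error. The protocol states neither, but either would raise power.

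The 20%–40% non-response figure looks as if it contradicts a 50% control rate. With no time point, it is weak support only, since the primary endpoint is at month 6.

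**Conclusion.** The point holds in conditional form. The stated source does not support 75% and 50% as arm rates, and no conversion is shown. On the plain reading, with an underdosed share of 54–69%, the arm difference is about 11–17 points. Power at N=130 is then about 26–36% with the reported sensitivities, or 36–55% with perfect targeting, against the stated 80%.

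This rests on three assumptions: that 50% and 75% are the two cohort groups' rates, that the share inferred from the performance figures applies to trial patients, and that extra doses at best restore the not-underdosed rate.

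A reader might go further and infer that the design cannot produce a 25-point difference, or that true power is about 50% or less. The documents do not support either: the cohort rates and the prevalence are not printed, the ceiling is not the protocol's, and the times to remission leave room for a larger gain in the higher-risk classes. What can be said is that the 80% requires a gain among patients treated differently well above 25 points, and the section neither states nor justifies one.

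**What to change.** In the Sample size section, derive both arm rates explicitly from:

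- the expected share of patients in each algorithm risk class;
- the algorithm's sensitivity and specificity;
- the expected month-6 remission in each class under each regimen.

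Then restate the power for N=130 under those rates, with a sensitivity range over the underdosed share and over the gain from extra doses. State the gain in the class above 50% risk that 80% power requires. If the cohort rates were already converted, print the group rates and the conversion.

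Two shortcuts should be avoided. Relabelling 75% vs 50% as the effect in the class above 50% risk repeats the substitution, because that class is not the underdosed group: in the reconstructed tables 48 of its 55 members (87%) are underdosed. Printing a single power of about 50% would assume perfect detection and fix a prevalence that the documents do not give.

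The cost is wording and probably a less favourable stated power. No extra patients are requested and no treatment rule changes.

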### Evaluation criteria

The primary endpoint is the clinical remission 6 months after the first rituximab infusion. Clinical remission is defined as a composite criterion, combining according to KDIGO guidelines: (1) complete clinical remission, defined as urinary protein/creatinine ratio (UPCR) <0.3 g/g in a morning spot urine sample and serum albumin >30 g/L and (2) partial clinical remission, defined as UPCR <3.5 g/g with a decrease >50% from baseline (ie, first rituximab infusion) and improvement or normalisation of serum albumin.

Secondary endpoints include complete clinical remission at month 12; partial clinical remission at month 12; immunological remission (ie, negative antibody titre by ELISA or negative indirect immunofluorescence) at month 3, month 6, month 9 and month 12; changes in proteinuria and albuminuria from baseline to month 3, month 6, month 9 and month 12; changes in serum creatinine and CKD-EPI estimated glomerular filtration rate from baseline to month 3, month 6, month 9 and month 12; changes in anti-PLA2R1 antibody ELISA titre from baseline to month 3, month 6, month 9 and month 12 (patients with PLA2R1-associated membranous nephropathy only); occurrence of anti-rituximab antibodies at month 3, month 6, month 9 and month 12; residual serum rituximab level at month 3 after the first rituximab infusion; recording adverse events related to treatment during study follow-up; changes in lymphocyte counts: B cells (CD19, transitional, mature and memory) and T cells (CD3, CD4, CD8 and T-Reg); changes in non-immunosuppressive antiproteinuric treatment during study follow-up; assessment of clinician satisfaction with the algorithm used to calculate the risk of rituximab underdosing (in the experimental group only); predictive rate (%) of the algorithm for rituximab underdosing in the control group; pharmacokinetics in all patients with serum creatinine and serum albumin levels, weight, anti-PLA2R1 and rituximab level at day 0, day 15, day 30, day 45, month 3 and month 6; and plasma cytokine levels after non-specific stimulation of innate and adaptive immunity cells in pg/mL (interferon (IFN)-γ, IFN-α, interleukin (IL)-12p70, IL-17A, IL-4, IL-5, IL-10, IL-1 and IL-6) at day 0 and month 6.

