**Methods:**

A multicentre, randomised, controlled, open-label, prospective superiority clinical trial will be conducted in 13 French hospitals. 130 consecutive patients with primary membranous nephropathy and active nephrotic syndrome will be randomised to either the standard protocol control group (two 1 g rituximab infusions on days 0 and 15) or the algorithm-driven rituximab treatment group. In the latter, the rituximab dose will depend on the algorithm-estimated risk of underdosing. Patients with an algorithm-estimated risk of underdosing ≤50% will receive 1 g of rituximab on days 0 and 15. Patients with an algorithm-estimated risk of underdosing between 51% and 75% will receive 1 g of rituximab on days 0, 15 and 30. Finally, patients with an estimated risk of underdosing >75% will receive 1 g of rituximab on days 0, 15, 30 and 45. The primary study outcome is the rate of clinical remission (complete or partial) at month 6 after treatment initiation. The secondary outcomes include clinical remission at month 12, immunological remission, proteinuria, albuminuria, serum creatinine, estimated glomerular filtration rate, phospholipase A2 receptor type 1 antibody titre, anti-rituximab antibody occurrence, lymphocyte count, serum rituximab level and related adverse events.

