**Trial registration number:**

NCT06341205 trial number. Registered on 2 April 2024.

Strengths and limitations of this studyThe artificial intelligence-based personalised rituximab treatment protocol in membranous nephropathy (iRITUX) trial is a multicentre randomised controlled trial conducted in 13 centres in France.The iRITUX trial is the first study to evaluate the value of artificial intelligence to guide treatment in membranous nephropathy.The iRITUX trial is not a double-blind trial due to the different treatment regimens, but the results will be analysed blinded to treatment allocation.

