## Methods and design

### Design

This is a parallel, two-arm, randomised, open-label, multicentre (13 sites in France), prospective study comparing the superiority and safety of an algorithm-guided rituximab regimen with the standard regimen in adult patients with membranous nephropathy. The study will last 7 years, with a 6-year enrolment period and 1 year of follow-up. An overview of the study is shown in figure 1.

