### Safety data

We will record any adverse medical events in the form of signs, symptoms, abnormal laboratory results or conditions that occur or worsen compared with the baseline. The study sponsor (Nice University Hospital) has purchased insurance for this trial and is responsible for reporting adverse events to the European Medicines Agency.

As rituximab (Truxima®) is an approved treatment by the European Medicines Agency and the US Food and Drug Administration, we do not anticipate significant or serious adverse events. As a result, a data safety monitoring board is not required during the trial.

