### Statistical methods

Our analysis strategy will consider two populations.

ITT population: all patients included in the control or experimental group, whether or not they completed the treatment schedule and had all the biological samples required by the protocol. For the ITT analysis, and in the case of a significant number of lost to follow-up patients (estimated to be 5% for the protocol) that would challenge the robustness of the result, the ‘last observation carried forward’ strategy will be used to impute the missing data for the primary objective.Per-protocol (PP) population*:* all patients enrolled in the study who completed the treatment schedule and had all the biological samples required by the protocol.

As indicated in the sample size calculation, three interim efficacy analyses will be performed. The aim of these interim analyses is to demonstrate the positive effect of increasing the rituximab dose according to the patient’s risk level on the remission rate in order to apply this algorithm as soon as possible.

To maintain the alpha risk at 0.025 with a beta risk equal to 0.2 for the final analysis and to limit the possibility of a chance of a positive interim finding, each interim analysis was planned with:

A one-sided significance level of 0.0002248 was allotted to the first efficacy interim analysis (n=44).A one-sided significance level of 0.00209 was allotted to the second efficacy interim analysis (n=66).A one-sided significance level of 0.00969 was allotted to the third efficacy interim analysis (n=98).A one-sided significance level of 0.02144 was retained for the final analysis (n=130).

The rate of clinical remission observed at 6 months from the first rituximab injection (primary outcome) in the two groups will be compared with access to the significance level, applying a one-sided test for the difference between two binomial proportions (χ^2^ test or Fisher’s exact test in case of a small sample). As the experimental and control groups differ only in the dose of rituximab, with a higher or equivalent dose in the experimental group, a two-sided test is unnecessary in our study.

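### The only adverse-event endpoint is limited to treatment-related events, so the open-label safety comparison is exposed to differential attribution although all events are recorded

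*Protocol article*

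**What the plan says.** Safety is a stated aim of the comparison. The Design section describes the study as "comparing the superiority and safety of an algorithm-guided rituximab regimen with the standard regimen".

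The list of secondary endpoints under Evaluation criteria has one adverse-event item: "recording adverse events related to treatment during study follow-up". The Methods paragraph of the Abstract carries the same restriction and ends its outcome list with "serum rituximab level and related adverse events". No listed endpoint counts adverse events whatever their cause.

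The Safety data section describes a wider collection: "We will record any adverse medical events in the form of signs, symptoms, abnormal laboratory results or conditions" that arise or worsen relative to baseline. Nothing there restricts recording to related events.

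On blinding, Design reads: "This is a parallel, two-arm, randomised, open-label, multicentre (13 sites in France), prospective study". The strengths and limitations list adds that the trial "is not a double-blind trial due to the different treatment regimens, but the results will be analysed blinded to treatment allocation". On exposure, Statistical methods says: "As the experimental and control groups differ only in the dose of rituximab, with a higher or equivalent dose in the experimental group".

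**The concern.** Whether an event is related to treatment is a judgement made after randomisation. In an open-label trial, a person making that judgement would normally know how many infusions the patient has had. If the share of events called related differs between arms for that reason, the related-event rates differ even when the true event rates do not, or agree when the true rates differ.

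The setting leaves real room for this. The Benefits section names immunodeficiency and thrombosis among the complications of persistent nephrotic syndrome, and the Risks section names infections among the reactions to rituximab. An infection could reasonably be assigned to either cause. The direction cannot be predicted. Knowing that extra infusions were given could raise attribution in the experimental arm. The article's stated expectation that further doses should not add risk could lower it.

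At stake is whether the trial can give a fair account of harm for a strategy that gives an equal or larger amount of drug. The filter would also tend to leave out thromboembolic, cardiovascular and renal events judged to come from the disease. Those are the events that the article expects earlier remission to reduce.

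**Working it through.** The article gives no adverse-event rate for this trial, no share judged related, and no safety margin or power, so there is no figure to reproduce. The check sets the sections side by side and then uses a simple product to show how the endpoint behaves.

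**Step 1: what is collected and what is an endpoint**

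| Section | Content | Limited to related events? |
|---|---|---|
| Design | Safety compared between regimens | No |
| Safety data | Any adverse event recorded | No |
| Evaluation criteria | Adverse-event endpoint | Yes |
| Abstract, Methods | Adverse-event outcome | Yes |

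The restriction appears in both places where outcomes are listed. Aim and data collection are wider than the endpoint.

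**Step 2: is the filter protected?** Treatment is open-label. Under Experimental strategy, patients receive 2, 3 or 4 infusions according to predicted risk; control patients receive 2. The only blinding described is of the analysis, which comes after relatedness has been judged and cannot blind that judgement. No blinded or independent causality assessment is described. Safety data states that a data safety monitoring board is not required. The data monitoring committee consists of research assistants who do on-site monitoring, with no adjudication role stated. The independent committee in Statistical methods is mentioned only for termination after a significant interim efficacy result.

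**Step 3: consequence, with hypothetical rates**

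Related-event rate = (rate of any event) × (share of events judged related). None of the inputs below comes from the document.

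| True rate, exp. vs control | Share judged related, exp. vs control | Related-event rate, exp. vs control | Endpoint difference | True difference |
|---|---|---|---|---|
| 40% vs 40% | 50% vs 50% | 0.40×0.50 = 20% vs 20% | 0 points | 0 points |
| 40% vs 40% | 60% vs 50% | 0.40×0.60 = 24% vs 20% | +4 points | 0 points |
| 40% vs 40% | 70% vs 50% | 0.40×0.70 = 28% vs 20% | +8 points | 0 points |
| 40% vs 40% | 40% vs 50% | 0.40×0.40 = 16% vs 20% | −4 points | 0 points |
| 50% vs 40% | 50% vs 50% | 0.50×0.50 = 25% vs 0.40×0.50 = 20% | +5 points | +10 points |
| 50% vs 40% | 40% vs 50% | 0.50×0.40 = 20% vs 0.40×0.50 = 20% | 0 points | +10 points |

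With equal attribution and equal true rates the endpoint shows no difference. With unequal attribution it can create a difference or remove one. The table shows the mechanism and is no estimate for this trial.

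**The case against.** The strongest reply is that the article does not prevent the better analysis. The endpoint is one item in a list that is not presented as exhaustive, and it is worded as an activity (recording). No safety test, summary measure or exclusion rule is given. Every adverse event is to be recorded, so a table of all events by arm remains possible. A journal article also leaves adverse-event tables and causality procedures to the full protocol and the SAP, neither of which is shown. Some laboratory endpoints relevant to harm (anti-rituximab antibodies, creatinine and estimated glomerular filtration rate, lymphocyte subsets) need no attribution. The contrast between arms is also diluted, because experimental patients at predicted risk of 50% or less receive two infusions, as controls do.

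Much of this stands, and it rules out three stronger readings that a reader might infer:

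- That the plan throws away an unbiased comparison. It does not: the events are recorded. Nor are all-event counts wholly free of bias, since open-label reporting can affect them too.
- That attribution will be made unblinded, as a stated fact. The article does not say who judges relatedness or how. This is an inference from the open-label design and the lack of any described blinded assessment, and the full protocol could provide one.
- That the distortion has a known size. Nothing in the document supports any particular gap in attribution.

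The reply does not remove the point that the restriction to related events is stated, twice, as the definition of the only adverse-event endpoint. That goes beyond an omitted detail, because an SAP normally implements the endpoints the protocol names. The laboratory measures do not replace counts of clinical events. If all events were chosen as the comparison only after the data were seen, that choice would be post hoc.

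**Conclusion.** The concern holds as a fault in the definition of one secondary endpoint. The adverse-event endpoint is narrower than both the stated safety aim and the data to be collected, and the narrowing depends on a judgement that no described procedure protects from knowledge of the arm. The comparison of harms is therefore open to differential attribution of unknown size and direction.

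This rests on two assumptions: that relatedness is judged by someone aware of the treatment given, and that the full protocol does not already define an all-event safety endpoint. If either fails, the point shrinks to a mismatch of wording between sections. The primary efficacy endpoint and the sample size are untouched. The change is worth making before the data are analysed, since the plan names safety as an aim and the remedy is easy.

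**What to change.** Bring the Abstract and Evaluation criteria into line with Safety data. Define the safety endpoint as all adverse events and all serious adverse events, with infections as a category, compared by randomised arm over study follow-up and regardless of attribution. Keep treatment-related events as a descriptive subset, and state who judges relatedness and whether that person knows the arm.

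No new data collection is needed, because the events are already to be recorded. The cost is the endpoint wording and slightly more tabulation.
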